### Sample size

The MoST study plans to recruit 1000 patients over three years. Thus, with a conservative retention and survival estimate of 75%, this is reduced to at fewest 469 patients. With this sample size estimate, assuming 15% of patients receive an actionable result and using a significance level of 0.05, this project: has 90% power to detect a mean change of 5.8 and 2.6 points on the Impact of Events scale for patients with actionable and non-actionable results respectively (paired t-test, SD = 15) [32] and a mean difference of 4.5 points between patients with actionable and non-actionable results; Multiple regression with at most 24 explanatory variables (including dummy variables) has 90% power to detect significant categorical variables with 5 categories (largest possible categorical variable) when that predictor explains greater than 3.6% of the residual variance, or to detect a continuous variable when it explains more than 2.3% of the residual variance. For patients with actionable results only (at fewest 70), at 80% power the minimum variance explained for continuous variables would be 12% of the residual variance, and 15% for binary predictors. For logistic regression when outcomes are on average equally likely the power to detect an odds ratio of 1.4 is 95% or 80% when the other covariates explain zero, or 37% of the outcome variance respectively. For only those with actionable results, there is 80% power to detect an odds ratio of 2.14 or greater if the other outcomes explain zero outcome variance.

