## Discussion

The PiGeOn study advances the field by identifying the knowledge, values, attitudes and coping strategies of patients with regards to TGP, determining how these, and other factors, predict subsequent cancer-related behaviour and psychosocial outcomes, and aligning these with current ethical norms. It will be the first Australian study to collect longitudinal data on cancer patients’ experience of TGP over time.

The trial experience of the first 100 patients revealed the unexpected finding that a significant proportion of the cohort was eligible for both this sub-study, and the twin psychosocial sub-study, which involved participants undergoing GGS. This group will be treated as a separate cohort, as they will be facing the combined challenges of uncertainty related to prognosis/treatment related outcomes of the MoST component, as well as the germline implications for identifying increased cancer risk for blood relatives. Previous research using hypothetical scenarios unsurprisingly suggests that patients with cancer have greater concerns about GGS than TGP. [5] This study will provide the opportunity to explore attitudes of patients who have elected to undergo both.

Methodological issues considered in the development of this study included the timing of the psychosocial assessments, including questionnaires. Timing was crucial in order to capture participant experiences and this was modified early based on data collected in the initial phase of the programme. Given it is expected that 5–10% of the cohort will have actionable somatic mutations, sampling for the qualitative component will be manipulated between baseline and follow-up 1 to allow for exploration of the reaction to both return and non-return of actionable results. The follow-up 1 cohort will be reassessed qualitatively at the subsequent follow-ups. It is recognized that there may be challenges in maintaining the follow-up of patients not receiving actionable results, although cancer populations are known to be highly motivated to contribute to research. [35] It will be important to capture the experience of having hopes of finding a novel cure raised in 100% of poor prognosis patients only to have them dashed in the at least 90% in whom nothing is found. [36]

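### The sample-size section assumes 15% actionable results and at least 70 such patients, but the Discussion expects 5–10%; on the stated 469 that is 23–47 patients, and the actionable-group power figures are too favourable.

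*Protocol article*

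**What the plan says.** All quotes are from the protocol article.

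- **Sample size, base number.** "The MoST study plans to recruit 1000 patients over three years", and "with a conservative retention and survival estimate of 75%, this is reduced to at fewest 469 patients".
- **Sample size, actionable share.** Power is computed "assuming 15% of patients receive an actionable result and using a significance level of 0.05".
- **Sample size, Impact of Events scale.** The project "has 90% power to detect a mean change of 5.8 and 2.6 points on the Impact of Events scale" in patients with actionable and non-actionable results respectively ("paired t-test, SD = 15"), and 90% power for a 4.5-point difference between the two groups.
- **Sample size, actionable-only models.** "For patients with actionable results only (at fewest 70"), the detectable share of residual variance at 80% power is given as 12% for a continuous and 15% for a binary predictor. An odds ratio of 2.14 is said to have 80% power.
- **Discussion.** "Given it is expected that 5–10% of the cohort will have actionable somatic mutations", the qualitative sampling is to be adjusted. Later in the same paragraph hopes are raised in all patients "only to have them dashed in the at least 90% in whom nothing is found".

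**The concern.** The 15% and the 5–10% cannot both be the planning expectation for the same cohort. The Discussion uses the lower rate to justify a design decision, the change in interview sampling, while the quantitative section stays at the higher one. The terms differ slightly (an actionable result in one place, actionable somatic mutations in the other), but if nothing is found in at least 90%, at most 10% can have an actionable finding.

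The figure of 70 is offered as a floor, yet on the stated 469 it lies above the whole range that the Discussion implies.

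Hypothesis 3 is at stake. It concerns patients who receive an actionable result and compares their hope, anxiety, fear of progression and depression with those of the other patients. The predictor models restricted to this group are at stake too. If the smaller group materialises, a null comparison could be read as coming from an adequately powered analysis when it did not.

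**Working it through.** **Inputs.** From Sample size: N = 469, SD = 15, alpha 0.05, actionable share 15%, and the stated detectable effects. From Discussion: actionable share 5–10%. Two assumptions are added. Tests are two-sided, which reproduces the stated paired figure. The SD of 15, given with the paired test, also applies to the between-group comparison.

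**Group sizes.** 0.15 × 469 = 70.35, which is the plan's 70. 0.10 × 469 = 46.9 and 0.05 × 469 = 23.5, so 47 and 23 are used. The non-actionable groups are then 469 − 70 = 399, 469 − 47 = 422 and 469 − 23 = 446.

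**Paired change, actionable group.** Detectable change at 90% power ≈ 15 × (1.960 + 1.282)/√n. At n = 70 this is 5.81, so the plan's 5.8 reproduces. The noncentral t gives 5.89, with 89% power at 5.8. The table uses the noncentral t.

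**Between groups.** Standard error = 15 × √(1/n₁ + 1/n₂), which is 1.94 for 70 v 399, 2.31 for 47 v 422 and 3.21 for 23 v 446. The stated 4.5 points does not reproduce at 70 v 399. It reproduces only for an equal split of 469 (234 v 235, 90% power).

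| Actionable share | n actionable | Power, 5.8-point paired change | Paired change detectable at 90% | Power, 4.5-point difference | Difference detectable at 90% |
|---|---|---|---|---|---|
| 15% | 70 | 89% | 5.9 | 64% | 6.3 |
| 10% | 47 | 74% | 7.2 | 49% | 7.5 |
| 5% | 23 | 43% | 10.6 | 29% | 10.4 |

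**Actionable-only linear regression, continuous predictor, 80% power.** Noncentral F with 1 numerator df, n − k − 1 denominator df for k predictors, and noncentrality n × f², where f² is the share of residual variance.

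- n = 70: f² = 0.115–0.117 for k from 2 to 24. This reproduces the stated 12%.
- n = 47: f² = 0.175–0.183 for the same k.
- n = 23: f² = 0.377 for k = 2, 0.405 for k = 10 and 0.465 for k = 15.

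The 15% for a binary predictor reproduces at n = 70 as a 2-df test (0.144–0.147). On that reading it becomes 0.220–0.236 at n = 47 and at least 0.489 at n = 23.

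**Actionable-only logistic regression, odds ratio 2.14.** The inputs are ln 2.14 = 0.761, outcomes equally likely, one standardised covariate, and no variance explained by the others. The simple approximation is power = Φ(0.761 × √(n/4) − 1.960).

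- n = 70: 89%. A Wald version with integrated information gives 76%, so the stated 80% lies between the two.
- n = 47: 74% (Wald 59%).
- n = 23: 45% (Wald 33%).

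Both approximations fall below 80% at either lower rate.

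**Figures that do not move.** The 2.6-point change in the non-actionable group is not worsened, because that group grows from 399 to 422–446. The full-cohort regression and logistic figures use all 469 patients and do not depend on the split.

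**Base number.** 0.75 × 1000 = 750, not 469; 469 equals 0.75 × 625. On 750, 5–10% gives 38–75, and 70 would need 70/750 = 9.3%.

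**The case against.** The strongest reply is that the article holds two unreconciled expectations and nothing shows that the lower one is right. That stands. A reader might infer that the 5–10% was observed early in the programme, because the same paragraph mentions data from the initial phase. The text ties those data to the timing of assessments, and the experience of the first 100 patients to the overlap with the germline sub-study. The 5–10% is simply expected, with no source. The point is therefore a conflict of assumptions, not evidence that overrides 15%.

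Three other stronger readings also fail.

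- A reader might say that a 24-variable model cannot be fitted to 23 patients. The limit of 24 is stated for the full-sample regression; the actionable-only sentence gives no count.
- A reader might quote a rise in detectable partial R² from 14.8% to 26%. That uses 24 covariates and a different noncentrality convention. On the scale that reproduces the plan's 12%, the rise to n = 47 is to about 17–18%.
- A reader might blame the whole 4.5-point shortfall on the lower rate. That figure already fails at 15%, because it matches only equal groups; the lower rate makes it worse.

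It is also fair to say that the article names knowledge, preferences, attitudes and values as primary outcomes, that hypotheses 1 and 2 concern all patients at baseline, and that the parent study sets recruitment. None of these depends on the split. Lastly, 469 is called a minimum, so 23–47 is a range of minima and inherits any error in 469.

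**Conclusion.** The contradiction is real and lies wholly within the article. On its stated 469, the rate in the Discussion gives 23–47 patients with actionable results, so 70 is not a lower bound. The power claimed for that group is not met even at the favourable 10% end: the paired comparison has 74% to 43% power instead of 90%, and the actionable-only regression and odds-ratio figures also fall short. The between-group comparison has 49% to 29% power for 4.5 points, of which the fall from 90% to 64% is a separate error already present at 15%.

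The sizes rest on N = 469, two-sided tests and an SD of 15 for both comparisons. If the base were 750, the group would be 38–75: the upper end would support the claims tied to 70, but 70 would still not be a minimum. The defect is confined to the actionable-group and between-group figures, hence to hypothesis 3 and the actionable-only models. It does not show that the study as a whole is underpowered.

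**What to change.** 1. State one expected actionable rate with its basis, and use it in both sections.
2. Correct or explain the base number, since 469 does not follow from 75% of 1000.
3. Restate the actionable-group and between-group figures at 5% and 10%, keeping 15% only as an optimistic case. Compute the between-group figure with the actual unequal group sizes.
4. Replace the minimum of 70 with the number implied by the reconciled rate and the corrected base.
5. Limit the actionable-only models to a small number of predictors, chosen from those named in hypothesis 5, that the resulting number can support. Fitting an interaction with result type in the full sample would not restore power, because effects specific to this group still rest on the same few patients.

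The cost is recalculation and wording; no new data or change in recruitment is needed. The downside is that the stated figures become less favourable, and results for the actionable group will have to be reported as imprecise.

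### The stated 90% power for a 4.5-point difference between actionable and non-actionable patients does not follow from the plan's own inputs: at 70 v 399 with SD 15 the detectable difference is 6.3 points, and power at 4.5 is 64%

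*Protocol article*

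**What the plan says.** The Sample size section of the protocol article starts from the parent programme's 1000 patients and says of the number after losses that "this is reduced to at fewest 469 patients". It sets the group split and error rate by "assuming 15% of patients receive an actionable result and using a significance level of 0.05". On that basis the claim is that the study "has 90% power to detect a mean change of 5.8 and 2.6 points on the Impact of Events scale"; the first figure belongs to the actionable group and the second to the non-actionable group, with the bracket "paired t-test, SD = 15". The same sentence extends the 90% power to "a mean difference of 4.5 points between patients with actionable and non-actionable results".

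Further on, the regression figures open with "For patients with actionable results only (at fewest 70", which fixes the smaller group. For that subset, with power now set at 80%, the section states that "the minimum variance explained for continuous variables would be 12% of the residual variance, and 15% for binary predictors".

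The Quantitative data analysis section names the t-test for comparing means of continuous outcomes. Table 1 schedules the Impact of Events Scale at T1 and T2 only.

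**The concern.** A comparison of two groups loses precision when the groups are very unequal, because the smaller group dominates the standard error. With 70 patients on one side, 4.5 points (0.30 SD) at 90% power looked too small.

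The figure bears on a named hypothesis. Hypothesis 3 expects patients with actionable results to have less cancer-related anxiety than those without, and the Impact of Events Scale is the measure of that construct. This is the only between-group difference in means for which the section gives power. If it is wrong, a reader of a null result will believe that a 4.5-point difference would have been missed one time in ten, when the plan's inputs imply more than one time in three.

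**Working it through.** **Inputs, all from the Sample size section**
- Analysed patients: 469.
- Actionable share: 15%, so 0.15 × 469 = 70.35, taken as 70 (the section's own number), leaving 399.
- SD: 15, the only one given.
- Significance level: 0.05. Sidedness is not stated; two-sided is taken as standard.
- Power: 90%, so z₀.₉₇₅ + z₀.₉₀ = 1.960 + 1.282 = 3.2415.

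**Step 1. Reproduce the paired figures.** Detectable change = SD × 3.2415 / √n.
- n = 70: 15 × 3.2415 / √70 = 5.81. The stated 5.8 is reproduced, which indicates that SD 15 and the 15% share are the inputs in use.
- n = 399: 15 × 3.2415 / √399 = 2.43 (2.44 by the t distribution). The stated 2.6 is not reproduced. It would need n = (15 × 3.2415 / 2.6)² ≈ 350.

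**Step 2. Between-group difference.** Detectable difference = SD × 3.2415 × √(1/n₁ + 1/n₂).

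| Split | Normal approximation | Noncentral t | Power at 4.5 points (normal / t) |
|---|---|---|---|
| 70 v 399 | 6.30 | 6.31 | 63.9% / 63.7% |
| 234 v 235 | 4.49 | 4.50 | 90.1% / 90.0% |

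For 70 v 399, √(1/70 + 1/399) = 0.1296 and 15 × 3.2415 × 0.1296 = 6.30. For power at 4.5, 4.5 / (15 × 0.1296) = 2.315; 2.315 − 1.960 = 0.355; Φ(0.355) = 0.639. The ratio 6.30 / 4.5 is 1.40, that is 0.42 SD against 0.30 SD.

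**Step 3. Does any variant at 15:85 return 4.5?**
- One-sided 0.05, 90% power: 5.70.
- Two-sided 0.05, 80% power: 5.46.
- One-sided 0.05, 80% power: 4.84.
- 750 patients (75% of 1000), two-sided, 90% power: about 5.0.
- 1000 patients, no losses: 4.31.
- 70 v 399 with a smaller SD: an SD of about 10.7 is needed.

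None of the variants that keep SD 15 gives 4.5.

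**Step 4. The variance-explained pair.** A continuous predictor and a binary predictor each use one degree of freedom in a linear regression. In the same model, with the same n and power, the minimum share of residual variance is therefore the same for both. The section gives 12% and 15% and does not say what differs between them.

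**The case against.** The strongest reply is that SD 15 sits inside the bracket for the paired test and so may be the SD of within-patient change; no SD is stated for the between-group comparison. A smaller between-group SD would rescue 4.5. If 15 is the SD of change from T1 to T2, a single-visit SD of 15/√2 = 10.6 gives 4.46 points at 70 v 399, but that requires zero correlation between visits in the same patient. Analysing the mean of the two visits gives an SD of 10.7 if the correlation is about 0.34, which is an assumption. The document states neither route. Adjustment for baseline is not available either, because the scale is not collected at T0. So the objection leaves room for a different SD having been intended, but it does not make 4.5 follow from what is written.

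Four stronger readings are tempting, and the documents do not carry them.
- **That the plan assumed a 50:50 split.** The match is very close (4.50 by the t-test), but the section never states or implies an equal split. It is a likely cause, not an established one.
- **That the 15% for binary predictors is a two-degree-of-freedom figure.** To get both 12% and 15% that way one must suppose 12 covariates, a number found nowhere in the document. One degree of freedom with the stated maximum of 24 explanatory variables and n = 70 also gives about 15%. All that can be said is that the pair is unexplained.
- **That the 2.6 overstates sensitivity.** It claims less than 399 patients would deliver, so it errs on the safe side.
- **That the study must be enlarged.** Holding 90% power at 4.5 points with a 15:85 split would need about 916 analysed patients. But the parent programme sets the sample size, the abstract names knowledge, preferences, attitudes and values as primary outcomes, and 4.5 is given as a detectable difference, not as an expected or minimally important one.

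It is also fair to say that 6.3 inherits inputs that are themselves unsettled. Seventy-five per cent of 1000 is 750, not 469, and the Discussion expects 5–10% of the cohort to have actionable mutations. With 469 patients and SD 15, 10% (47 v 422) gives 7.5 points and about 50% power at 4.5; 5% (23 v 446) gives 10.4 points and about 29%.

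**Conclusion.** The between-group power statement is wrong as written. On the section's own inputs the comparison has 90% power for 6.3 points, not 4.5, and 64% power for 4.5, not 90%. This rests on SD 15 applying between groups, a two-sided test and a plain two-sample comparison. A one-sided test raises power at 4.5 only to 75%.

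The paired 2.6 is a small, conservative slip (2.4 at n = 399). The 12% and 15% pair is inconsistent if both refer to the same model, but its cause cannot be read from the document.

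Severity is moderate. The figure misstates the power of a named hypothesis test, but on one scale that is not a primary outcome, and no recruitment decision depends on it.

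**What to change.** In the Sample size section:
- Replace the between-group figure by 6.3 points at 90% power, or say that power for 4.5 points is 64%. If a between-group SD other than 15 was intended, give it with its justification and name the analysis it belongs to; about 10.7 is what 4.5 points requires.
- State that the test is two-sided, if it is.
- Change the non-actionable paired change from 2.6 to 2.4 points, or give the n that was used.
- Give one minimum variance for continuous and binary predictors in the actionable subset, or state the different models behind 12% and 15%.
- Before printing the new figure, confirm the 469 and the 15% against the 75% retention estimate and the 5–10% in the Discussion, since the detectable difference moves with both.

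The cost is wording and a short recalculation. No extra patients are needed; the between-group figure becomes less favourable.

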## Methods/design

### Aims and hypotheses

The aim of this study in adults with advanced cancer undergoing TGP is to:*Before and after receipt of results:* evaluate knowledge of TGP, preferences for genetic information, attitudes (positive and negative) and the value placed on TGP;*After receipt of results:* identify behavioural, decisional and psychological outcomes from TGP along with their respective predictors; andContextualize the findings via a critical bioethics analysis.

Specific hypotheses are that:At baseline (after giving informed consent to undergo TGP), advanced cancer patients will have moderate to poor knowledge about TGP (< 55% correct on knowledge scale).At baseline, advanced cancer patients will have primarily positive attitudes to, and highly value, TGP.Of advanced cancer patients *who receive an actionable result*, most will:Pursue personalised treatment in a clinical trial setting (behavioural outcomes).Cope well with results, and experience low decisional conflict and regret and high decisional satisfaction (decisional outcomes).Have higher hope, less cancer-related anxiety, lower fear of cancer progression and lower general anxiety and depression than those who do not receive actionable results (psychosocial outcomes).Those advanced cancer patients who have *no actionable variants identified* will:Struggle to cope with non-results (decisional outcomes).Have levels of hope, cancer-related anxiety, fear of cancer progression and general anxiety and depression similar to published results for advanced cancer patients who have not undergone TGP, within 1 month of receiving results and 5 months later (psychosocial outcomes).5.Predictors of behavioural, decisional and psychological outcomes within 1 month of receiving results and 5 months later, will include:Age, education level, ethnicity, and gender;Tolerance of uncertainty and baseline knowledge; andPreferences and attitudes to TGP.

Methodology in critical bioethics analysis is not hypothesis-driven and to this end there are no hypotheses relating to this part of the analysis.

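### The stated 4.5-point detectable difference between actionable and non-actionable patients does not follow from the plan's own inputs; at 70 v 399 and SD 15 it is 6.3 points

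*Protocol article*

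**What the plan says.** The Sample size section starts from the parent programme's 1000 recruits and, after allowing for retention and survival, says that "this is reduced to at fewest 469 patients". The power statement then proceeds "assuming 15% of patients receive an actionable result" and "using a significance level of 0.05". In one sentence it claims 90% power for three effects on the Impact of Events scale:

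- a within-patient mean change of 5.8 points in the actionable group;
- a within-patient mean change of 2.6 points in the non-actionable group, both labelled "paired t-test, SD = 15";
- "a mean difference of 4.5 points between patients with actionable and non-actionable results".

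The size of the smaller group is confirmed further on: "For patients with actionable results only (at fewest 70". No SD other than 15 is given, and no correlation or covariate adjustment is stated for the between-group comparison. The Quantitative data analysis section names a t-test for comparing means of continuous outcomes.

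**The concern.** With a fixed total, a two-group comparison loses precision as the split becomes more unequal. A 15:85 split of 469 patients is far from equal, so its detectable difference should be well above that of a balanced comparison. A figure as small as 4.5 points, next to 5.8 points for a paired test in the 70 actionable patients, looked too small for an SD of 15.

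The contrast matters because part of hypothesis 3 is comparative. It expects patients with actionable results to have higher hope and "less cancer-related anxiety, lower fear of cancer progression and lower general anxiety and depression than those who do not receive actionable results". The 4.5-point figure is the only power stated for a two-group difference in means on any of these outcomes. If it is too favourable, a non-significant result could be read as evidence against a 4.5-point difference when the study had a sizeable chance of missing one.

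**Working it through.** **Inputs (Sample size section).** Total 469. Actionable share 15%: 0.15 × 469 = 70.35, so 70 v 399. Alpha 0.05, power 90%, SD 15. Sidedness is not stated. Two-sided is taken because only that reproduces the paired 5.8 (one-sided gives 5.2). The multiplier is 1.960 + 1.2816 = 3.2415. The 469 is taken as given.

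**Paired figures.** Detectable change = 3.2415 × SD / √n.

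- n = 70: 3.2415 × 15 / 8.367 = 5.81. This matches the stated 5.8 (5.9 with the noncentral t).
- n = 399: 3.2415 × 15 / 19.975 = 2.43 (2.44 with the noncentral t). The stated value is 2.6, which corresponds to n = (3.2415 × 15 / 2.6)² ≈ 350.

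**Between-group figure.** Detectable difference = 3.2415 × SD × √(1/n₁ + 1/n₂).

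- √(1/70 + 1/399) = 0.1296, so the standard error is 15 × 0.1296 = 1.944.
- Detectable difference = 3.2415 × 1.944 = 6.30 (noncentral t: 6.31).
- Power for 4.5 points: 4.5 / 1.944 = 2.315; Φ(2.315 − 1.960) = Φ(0.355) = 63.9% (noncentral t: 63.7%).
- Ratio to the stated figure: 6.3 / 4.5 = 1.40.

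**Can any nearby choice give 4.5 at SD 15?**

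| Setting | Detectable difference |
|---|---|
| 70 v 399, two-sided, 90% | 6.30 |
| 70 v 399, one-sided, 90% | 5.69 |
| 70 v 399, two-sided, 80% | 5.45 |
| 70 v 399, one-sided, 80% | 4.83 |
| 70 v 350 (the n implied by 2.6), two-sided, 90% | 6.37 |
| 113 v 637 (N = 750), two-sided, 90% | 4.96 |
| 150 v 850 (N = 1000), two-sided, 90% | 4.31 |
| **234 v 235 (equal split of 469), two-sided, 90%** | **4.49** |

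Only the equal split of 469 returns the stated value; its power for 4.5 points is 90.1%. At 15:85 and SD 15, 90% power for 4.5 points would take about 920 patients (137 v 783).

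**Which SD would give 4.5 at 70 v 399?** 4.5 / (3.2415 × 0.1296) = 10.7. Adjustment for a covariate correlated at about 0.70 with the outcome would produce it, since 15 × √(1 − 0.70²) = 10.7. The article states no such adjustment, and Table 1 shows that the Impact of Events scale is not collected at baseline, so there is no baseline score to adjust for.

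**The case against.** The strongest reply is that SD 15 is attached in the text only to the paired test, so the between-group SD is strictly unstated. This stands in part: 6.3 points and 64% hold if 15 also applies between groups. If 15 is the SD of change, comparing changes between groups still uses 15 and gives 6.3. If single scores are compared, their SD is 15 / √(2(1 − r)), where r is the correlation between the two follow-ups, for which the article gives no figure. Taking r as an assumption, the detectable difference is 4.5 at r = 0, 5.3 at 0.3, 6.3 at 0.5 and 8.1 at 0.7, with power for 4.5 points of about 90%, 78%, 64% and 43%.

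A reader might infer from this that the authors assumed uncorrelated follow-up scores. The documents do not support that: the equal-split route reaches 4.5 from the stated N and SD with no correlation at all.

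A reader might also see a contradiction with the regression clause, "or to detect a continuous variable when it explains more than 2.3% of the residual variance". At SD 15, a 4.5-point difference explains (70/469)(399/469)(4.5/15)² = 1.1% of variance, below 2.3%. But the 1.1% is a share of total variance in an unadjusted comparison, while the 2.3% is a share of residual variance in a regression with up to 24 explanatory variables. If the other variables explained half the variance, 1.14% of the total would become about 2.3% of the residual. The comparison also presupposes SD 15, so it adds no independent evidence.

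Finally, it can be said that little depends on the figure. The abstract names knowledge, preferences, attitudes and values as primary outcomes, the Impact of Events scale is one of several psychological outcomes, and the parent programme sets the sample. All of this stands and limits the weight of the point, but it does not make the figure right.

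**Conclusion.** The 4.5-point claim is wrong on the inputs the section gives. At 70 v 399, SD 15 and two-sided 0.05, the detectable difference at 90% power is 6.3 points. Power for 4.5 points is about 64%, so the chance of missing such a difference is about 36% rather than 10%. The error is in the optimistic direction.

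This rests on taking 15, the only SD in the section, as the between-group SD, and on a two-sided test. That the 15:85 split was left out of the calculation is the likeliest cause, because the equal split reproduces the figure, but it remains an inference.

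It would be too strong to say that the study's design or sample size is unsound because of this. The contrast is not a primary outcome and does not determine recruitment. The point is a wrong stated figure that should be corrected. A smaller slip sits in the same sentence: the paired figure for non-actionable patients is 2.4 at n = 399, so the stated 2.6 is slightly conservative.

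**What to change.** In the Sample size section, replace the between-group figure of 4.5 points by 6.3 points at 90% power, or keep 4.5 points and state that its power is about 64%. Give the group sizes (70 v 399), the SD and the sidedness beside the figure. If a between-group SD other than 15 was intended, state it with its basis and derive the detectable difference from it at 70 v 399. Recompute the paired figure for non-actionable patients in the same pass: 2.4 points at n = 399 and SD 15, or state the group size that gives 2.6.

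The cost is one revised sentence and a less favourable stated figure for the two-group comparison. No extra patients are needed, and the analysis does not change.
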